### Pubertal staging

The evaluation of the pubertal stage is made by the student’s self-evaluation method from a table with images of the five pubertal stages of Tanner, according to gender [35]. For girls, the board is presented with staging for breasts (M) and pubic hair (P). For boys, the plank contains of staging of the external genitalia (G) and pubic hair (P). The evaluation is done individually and the student is asked to point out his stage according to his perception. This evaluation is carried out in a quiet and reserved environment, solely in the presence of the evaluator.

### Evaluation of the quality of life and religiosity

The quality of life is evaluated through the Pediatric Quality of Life Inventory questionnaire - PedsQL ™ 4.0 (ages 8–12 years) validated to Portuguese [36, 37]. For its application, a properly trained researcher invites each student individually to a quiet environment to answer the questionnaire at school. The researcher reads the questions and takes personal notes after an oral response of the student. This methodology was used as this questionnaire contains some questions that are difficult for students with poor schooling abilities to understand. The questionnaire has four areas: (a) health evaluation by assessing the difficulties that the student encounters when performing activities such as running, walking, bathing, carrying something heavy, pain or lack of energy; (b) problems with feelings (scared, sad, angry, sleeping difficulties, worries about the future); (c) problems about how to get along with others; and (d) problems about performance at school.

A growing number of studies have shown that religiosity, although it does not have a direct action on physical health, influences strongly psychological well-being and adherence to treatments. For this reason, the student’s religious practice is being investigated. The results will be evaluated in relation to adherence to the proposed protocol and performance during treatment. A religious scale developed by researchers from the American University of Duke, the Duke Religious Index (DUREL), validated for the Brazilian population, is being used [38, 39]. This questionnaire is being applied by a properly trained interviewer in a quiet environment. The interviewer reads the questions, explains the meaning of the words to the student if necessary, and registers the answers him/herself. The instrument accesses the three major dimensions of religiosity: organizational and non-organizational religious activities and intrinsic (subjective) religiosity [39].

### Evaluation of food addiction and eating attitudes

The Children’s Eating Attitudes Test (ChEAT) validated to Portuguese for this age group is used for the evaluation of abnormal eating attitudes and behaviors [40, 41]. The questionnaire has three domains: (a) food preoccupation, (b) restrictive and purgative behaviors and (c) oral control. A trained dietitian is responsible for applying the questionnaire at school. The questionnaire is applied in two students at the same time. The students are separated so that they are not able to see one another and are instructed not to read their answers aloud. Each application lasts about 45 min. The students receive the questionnaires and a pen to mark the response. The lines are alternated with white and gray lines to make it easier for the student to follow the line and not mark the answer to the wrong question. The researcher reads each question, while the students follow the reading in their own questionnaires. To ensure the quality of the application and avoid bias through tiredness and repetition, up to 10 students are invited to answer the questionnaires each day. This information will aid the dietitian in charge of the outpatient consultations to assist the student in behavior change and to create strategies that can help the nutritional recovery process.

The protocol also includes the use of the Yale Food Addiction Scale (YFAS) [42] that is applied in exactly the same way as the Children’s Eating Attitude Test. This scale has not been validated in Brazilian children and the researchers extended the translation to Portuguese. The results will be compared with all the other information collected in this intervention protocol.

### Transtheoretical model test

The readiness for change of the students is being evaluated according to the Transtheoretical Model test. This test addresses five stages of behavior: pre-contemplation, contemplation, preparation, action, and maintenance [20, 43]. The main characteristic of the pre-contemplation stage is the lack of willingness to change. This stage is characterized by a resistance to acknowledge the error and to modify it. Those in the contemplation stage are aware of their problem and are seriously considering changing the behavior but have not yet taken any initiative, do not know where to start, or do not feel prepared to change. In the preparation stage, the subject wants to change behavior in near future, claims to be motivated, and sees that change may occur in the following months. The action stage involves a previous occurrence of a behavioral and/or environmental change. Subjects at this stage underwent real experiences to stop the problem and have overcome previously perceived barriers. The maintenance stage occurs when the subjects have changed their behavior for more than six months, and the intervention aims to maintain the habits acquired. The questionnaires with the food behavior and physical activity algorithms are applied exactly in the same way as the Eating Attitude Test described before. This information will aid the dietitian during the outpatient consultations.

### Figure rating scale

Body image is closely linked to the development of eating disorders and quality of life and is a determining factor for readiness to change food behavior. The usual method of evaluation is the scale of silhouettes ranging from the leaner to the more obese [44]. The scale has several advantages, since it is easy to apply (it can be self-applied), it does not require a great diversity of verbal fluency and it is an inexpensive and didactic instrument, which makes it particularly suitable for the evaluation of the perception of the corporal image, mainly of children [44]. In the case of children, the great concern is the suitability of the scale figures for children’s silhouettes from other countries; therefore, a Brazilian silhouettes scale was used for children from 7 to 12 years of age. The scale was applied at the same time as the other questionnaires at school.

### Food consumption

A Semiquantitative Food Frequency Questionnaire (SFFQ) was used for the estimation of long-term dietary intake [45]. This method also allows the estimation of the amounts ingested per unit of time (day, week, or month). Energy and nutrients are calculated according to the frequency of consumption [45, 46].

The Brazilian SFFQ for adolescents was developed and validated in Rio de Janeiro in 2010 [45]. The questionnaire was pre-tested with 10 adolescents (written informed consent, was obtained from these participants and their parents/legal guardians) living in the same region of the present study, in order to evaluate if the foods that make up the list were included in the habitual repertoire of the population of São Paulo. Simultaneously, we also analyzed the time required for the application of the questionnaire and the receptivity of the adolescents in relation to the research protocol. Before application, the questionnaire was evaluated by the team of dietitians at CREN and was modified and adapted to account for the differences in regional nomenclatures, with inclusion and exclusion of very infrequent food items.

The computer was chosen for data collection. The same interviewer applied the questionnaire individually. A Photo Manual was used to assist recording the portion sizes [46]. To avoid bias due to fatigue and repetition, SFFQ was applied in a maximum of 8 students per four-hour period. Data from the food records will be converted to energy and nutrients using the Nutrition Data System for Research (NDS-R version 2012, University of Minnesota) software.

### Socioeconomic data collection

The collection of information on the socioeconomic profile of the student is performed at CREN during outpatient visits, in order to gain an insight into the student’s family conditions and the environment at their place of residence. Information on the student’s family composition, parents’ level of education, and family income are also registered.

### Outcomes

Recovery of BMI (BMI < 1) or a persistent and progressive reduction in BMI throughout the intervention period will be considered as the primary outcome.

Furthermore, the following are the secondary outcomes expected: reduction of waist and neck circumferences, reduction in body fat percentage, reduction in blood pressure, and improvement of the biochemical profile. The following improvements in social variables are also expected: in the proportion of overweight students motivated to maintain healthy eating habits and in achieving the stablished goals, in the proportion of those motivated to maintain physical activity recommendations, on the average quality of life index, in the proportion of students with a positive body image, recovery of the symptoms of food addiction, and the social network communications regarding excess weight.

### Exclusion criteria

Overweight students of both control and experimental groups were excluded from the data collection if they were reported to have cognitive delay, as per their parents and/or teachers, which could limit their involvement in activities such as answering questionnaires. In addition, were excluded those with motor limitations, twins, those taking medications known to affect body weight management, and those with any known family issues that could affect the overall compliance and participation in the Program.

### Analysis plan and statistics

The data will be tabulated with double input. Descriptive statistics will be used to correlate all variables, by using mixed analysis models. Adjustments will be made for age, gender, pubertal stages using IBM Statistical Package for Social Sciences (SPSS Statistics Desktop) base 22.0.

Changes in the outcomes will be evaluated using a fixed-effects model, and covariate adjustment will be performed to account for the difference in sizes between both groups. Missing data will be identified in each subgroup. An imputation model based on the Multiple Imputations by Chained Equations (MICE) method will be applied (package MICE 2.25, running on R version 3.3.2) [47]. The imputation model will include all the baseline features in addition to age, gender, and classroom. According to this method, a suitable number of imputation models to account for a 95% CI is 59 (we will assume a worst-case scenario and use the maximum missing proportion). Regarding the number of iterations, as suggested in [48], we will use 5 iterations and the Predictive Mean Matching (PMM) method for every outcome variable. After generating imputed models, they will be pooled according to Rubin’s rule in order to obtain valid statistical inferences [49].

Changes in remission, incidence, and prevalence of obesity in the experimental group and control will be evaluated at the end of the study. Odds ratios adjusted for age, gender, and other baseline measures will also be calculated.

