### At school

All students of the 3rd, 4th, and 5th grades participate in the activities in their respective classrooms (Fig. 1). The intervention groups consist of weekly reflective meetings conducted by the psychologist, nutrition education workshops conducted by two dietitians, and physical activities supervised by the specific physical educator of the project in addition to the routine classes of physical activity included in the school curriculum. Further, the research team holds monthly meetings focusing on nutrition education and improved lifestyle for families and students. The following activities are held during these meetings: nutrition workshops, reflective meetings, and physical exercise. Teachers participate in the entire program as collaborators, favoring the youth participation in the proposed activities. Specific monthly meetings are also being conducted for teachers. Moreover, the project team is available to all teachers who wish to receive individualized nutritional care, offering anthropometric and body composition evaluations and nutrition advice.

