### Description of the activities at school

**Reflective Meeting**
The reflective meeting is a psycho-educative group activity for seeking solutions and alternatives for common and significant issues of the existence. The theoretical base of this practice is the existential phenomenology and the dialogical group meetings proposed by Paulo Freire [18]. This approach was chosen because the phenomenological exploration in psychology allows a broad understanding of the human experience, with a focus on the meanings, motivations, and decisions for actions. According to *Van Manen & Adams*, it can allow the participants to suddenly see or grasp a human phenomenon in a way that enriches their understanding of everyday life experiences. Such a sudden insight may transform their being and, therefore, their practices [19]. The present protocol employed this methodology as the result of years of experience at CREN regarding treatment in complex environments, such as families facing many difficulties in their relationships. The reflective meeting provides an atmosphere to build new paths for the issues discussed and to explore, by exchanging experiences, better living practices on a daily basis.The meetings occur weekly in groups of about 35 students at a time and last 45 min. Examples of the themes discussed are presented in Table 1. Each theme has been designed to meet the demands identified in their daily life. The psychologist coordinates the group activities in cooperation with another professional aid, who records key information during the sessions. This activity is also being conducted with parents/guardians and teachers.The meetings are designed in accordance with the structure suggested by Szymanski [18], with the following steps: planning, preparatory activity, reflection focused on the demand, and final synthesis.

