#### Control group

##### 2.9.1.1.At school

The students in the control group (*n* = 353) participate in weekly meetings with the whole class for the first six months, with the purpose of motivation for adopting a healthy lifestyle (Fig. 1). All students of the 3rd, 4th, and 5th grades participate in these activities. Weekly reflective meetings were conducted by the psychologist, as well as nutrition education workshops led by the two dietitians. In addition, three meetings are held with parents and teachers where the following activities are performed: the importance of having a healthy lifestyle, eating breakfast, and teaching healthy recipes. After this motivation period, all overweight students were referred for outpatient treatment at CREN.

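### The outcome model is called a fixed-effects model and no between-arm analysis carries a classroom term or cluster-robust error, although sessions are delivered by class in both schools

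*Protocol article*

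**What the plan says.** All references are to the Protocol article.

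- **Outcome model** (Analysis plan and statistics): "Changes in the outcomes will be evaluated using a fixed-effects model". Covariate adjustment is added for the difference in group sizes.
- **Covariates** (same section): "Adjustments will be made for age, gender, pubertal stages". Classroom is not among them. The odds ratios are adjusted for age, gender and other baseline measures, again without any mention of classroom.
- **The other model named** (same section, two sentences before the outcome model): "Descriptive statistics will be used to correlate all variables, by using mixed analysis models". No random effect is given.
- **Where classroom appears** (same section): "The imputation model will include all the baseline features in addition to age, gender, and classroom". This is its only appearance in the analysis section.
- **Delivery in the experimental school** (At school): "All students of the 3rd, 4th, and 5th grades participate in the activities in their respective classrooms". For the reflective meetings: "The meetings occur weekly in groups of about 35 students at a time and last 45 min". The nutrition workshops also use groups of 35, and physical activity uses groups of about 35 to 40.
- **Delivery in the control school** (Control group, At school): students "participate in weekly meetings with the whole class for the first six months".
- **Allocation** (Study population): one school per arm, 438 and 353 students, not randomised.

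**The concern.** Children in one class share the same sessions, teacher and peers, and the Background gives the influence of the whole classroom as a reason for the approach. Some within-class correlation in weight change is therefore to be expected. A student-level model with fixed effects only puts that shared variation into the residual as if it were independent. The between-arm standard error is then too small and the p-value too low. The error runs towards a false claim of benefit, and the Discussion expects the results to contribute to public policy.

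**Working it through.** **1. The plan's own sample size.** Inputs from Sample size calculation: difference 0.12, spread 0.30 (called a standard error, but it works only as a standard deviation), alpha 0.05, power 0.80.

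n per group = 2 × [0.30 × (1.960 + 0.842) / 0.12]² = 98.1, against the stated 98. The figure reproduces with a two-sided test and independent students. It contains no allowance for clustering.

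**2. What the possible readings of a fixed-effects model would do.**

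- *Regression on students with arm and covariates.* This ignores class.
- *Class dummies on change scores.* Classes are nested within arm. With 12 and 10 classes the design matrix has rank 22 both with and without the arm column, so the arm effect cannot be estimated.
- *A fixed effect for each student over time.* This removes stable differences between students, but class-level variation in change stays in the error term unless cluster-robust errors are used. None are named.

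No reading gives both an estimable arm effect and standard errors that allow for class.

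**3. Cluster sizes.** The number of classes is not stated. Assuming 35 eligible students per class, 791 / 35 = 22.6, about 23 classes.

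- Students with excess weight: 138 + 125 = 263, and 263 / 22.6 = 11.6 per class. This group serves the change in BMI z score and remission. It also serves prevalence, because Outcome measures defines prevalence by those who remained overweight or obese.
- Incidence: Outcome measures restricts it to students not overweight or obese at the start. 791 − 263 = 528, and 528 / 22.6 = 23.4 per class.

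**4. Effect on a nominal 5% test.** The ICC is not in the documents; 0.01, 0.02 and 0.05 are assumed. With m students per class, DE = 1 + (m − 1) × ICC and actual alpha = 2 × [1 − Φ(1.96 / √DE)].

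| Comparison | m | ICC | DE | Actual type I error |
|---|---|---|---|---|
| Excess-weight cohort | 11.6 | 0.01 | 1.11 | 6.2% |
| | | 0.02 | 1.21 | 7.5% |
| | | 0.05 | 1.53 | 11.3% |
| Incidence | 23.4 | 0.01 | 1.22 | 7.6% |
| | | 0.02 | 1.45 | 10.3% |
| | | 0.05 | 2.12 | 17.8% |

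**5. Simulation check.** With 20,000 runs, 12 against 10 classes of 12 students and no true effect, a student-level test of change rejected in 5.1%, 6.2%, 7.5% and 11.4% of runs at ICC 0, 0.01, 0.02 and 0.05. A test on class means stayed between 4.8% and 5.0%.

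**6. Sensitivity to the class count.** Study population gives 1003 children enrolled in the age group. If the ineligible children sit in the same classes, there are 1003 / 35 = 28.7 classes and 263 / 28.7 = 9.2 students with excess weight per class. The actual type I error is then about 6.0%, 6.9% and 9.9%.

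**The case against.** The strongest reply is that the article never says students are treated as independent. It gives a model label without error structure, and a condensed article may leave random terms to a fuller document. That is fair as far as it goes. But the article does name the outcome model, lists covariates and gives imputation settings down to the number of iterations. It puts classroom in the imputation model and not in the outcome model. A reader who follows the text would leave clustering out.

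Other points on that side:

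- A reader might infer that the section flatly contradicts itself, mixed against fixed. The text does not support that. The mixed models are attached to descriptive and correlation work, and the fixed-effects model to outcome changes. The wording is unreconciled. Because the mixed sentence names no random effect, it does not rescue the outcome analysis either.
- A reader might apply 35 students per class to incidence and prevalence and report a type I error of 9%, 13% and 23%. The definitions in Outcome measures rule this out. Those figures fit only a comparison of all students, such as the overall nutritional profile.
- The inflation needs a positive ICC and is modest at 0.01. Part of the care for students with excess weight is given at the outpatient centre, and the control school's class sessions last only six months, so a small ICC is possible.
- Remission, incidence and prevalence have their own paragraph, so the fixed-effects sentence does not cover them directly. That paragraph names no clustering method, so the gap is the same.
- With one school per arm, a classroom term cannot protect against a school effect. This stands, and it limits what the correction can claim.

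**Conclusion.** The point holds for the classroom level. The named analysis, followed as written, allows for no within-class correlation in any between-arm comparison. Under an assumed ICC of 0.01 to 0.05 and about 23 classes, the type I error of a nominal 5% test is about 6.2% to 11.3% in the excess-weight cohort and about 7.6% to 17.8% for incidence. With no within-class correlation there is no inflation, and with more, smaller clusters it is lower.

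A reader might infer that a classroom term would make the between-arm p-values fully valid. It would not. School and intervention coincide, and no analysis of two schools can separate them. The classroom part is what the analysis can correct, and it is worth correcting because the identifier is already held.

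**What to change.** - Name one model for outcome change: a linear mixed model with arm and covariates as fixed effects, a random intercept for baseline classroom, and small-sample degrees of freedom (about 23 − 2 = 21 between classes).
- For remission, incidence and prevalence, use a logistic mixed model with the same random intercept, or cluster-robust GEE with a small-sample correction.
- Reconcile the sentence on mixed models with this, so that one model clearly governs the outcomes.
- State that with one school per arm the school effect cannot be separated from the intervention, so p-values and intervals account for classroom-level clustering only.

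**Cost.** A few lines of code, using an identifier already held. Intervals widen by √DE: from √1.11 = 1.05 to √1.53 = 1.24, or about 5% to 24%, in the excess-weight cohort. For incidence the widening is from √1.22 = 1.11 to √2.12 = 1.46, or about 11% to 46%. The plan does not say whether classes stay together for 16 months, so baseline classroom should be named as the cluster and any later mixing reported.

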**Methods/study design:**

The study was conducted by the Center for Recovery and Nutritional Education (CREN) in São Paulo, Brazil. Two schools located in poor neighborhoods were selected for the intervention, between March 2016 and June 2017. The participants were all students aged 8 to 12 years from the two participating schools. At the beginning of the intervention, anthropometric measurements were carried out to assess the nutritional status of the students. For convenience, students from one of the schools were considered as the control group, while those from the other school formed the experimental group. The intervention in the experimental group (*n* = 438) consists of the following weekly activities at school: psychological counseling in groups, theoretical/practical nutrition workshops, and supervised physical education classes. In addition, theoretical and practical educational activities are held regularly for parents, teachers, and cooks. Students with excess of weight (≥1 body mass index [BMI] –for-age Z score, *n* = 138) received clinical and nutritional care periodically at the outpatient care at CREN. Students enrolled in the control group (*n* = 353) participated in psychological counseling groups and theoretical/practical nutrition workshops for 6 months held in the school environment to provide motivation to entire classrooms. In the following 10 months, students with excess of weight from the control group (*n* = 125) were invited to attend the routine outpatient care at CREN.

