## Methods

### Study design

This is a controlled, prospective trial aimed at investigating the effectiveness of a 16-month, multi-component, and environmental school-based intervention for recovery of poor income overweight/obese students in which subjects are not randomly allocated. This study design was chosen since evidence increasingly has shown that randomized control trials (RTC) are not the most suited models to test the complex and chronic care required to treat children and adolescents with excess weight [15]. Moreover, the present design does not allow randomization of control and experimental groups, since the intervention involves the entire school environment.

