### Study population

Two schools were chosen for this study among the three existing schools of the Southeast area of the city of São Paulo, Brazil. The schools have similar teaching schedules, are located in poor neighborhoods, and have students from equivalent socio-economic backgrounds. The selection criterion was their geographical location or proximity to the Center for Recovery and Nutritional Education (CREN), from where the Program is being managed. In all, 1003 children of the defined age group were enrolled in the two schools. After the first analysis, it was verified that 213 children did not meet the inclusion criteria, reducing the number of eligible participants to 791. The study included all the students between 8 to 12 years of age (*n* = 791) enrolled in the two schools. One school was chosen as the experimental group (*n* = 438), and the other was the control group (*n* = 353).

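### Covariate adjustment in the model for change is justified by unequal group sizes, which need none; the baseline value of the outcome is not a named adjuster in this non-randomised two-school comparison

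*Protocol article*

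**What the plan says.** Under Analysis plan and statistics, the protocol article plans a fixed-effects model for changes in the outcomes and gives one purpose for its covariates: "covariate adjustment will be performed to account for the difference in sizes between both groups". The general statement on adjusters is "Adjustments will be made for age, gender, pubertal stages". For the binary outcomes it adds "Odds ratios adjusted for age, gender, and other baseline measures will also be calculated", without listing those measures. A wider set of baseline variables appears only for missing data: "The imputation model will include all the baseline features in addition to age, gender, and classroom".

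The Study design section describes a trial "in which subjects are not randomly allocated", and the abstract says "For convenience, students from one of the schools were considered as the control group". Study population states that the two schools "have students from equivalent socio-economic backgrounds" but gives no data. According to Socioeconomic data collection, "The collection of information on the socioeconomic profile of the student is performed at CREN during outpatient visits".

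BMI-for-age z is measured at the start and end of the intervention (Data collection, Weight and height). It underlies the primary outcome and the sample size calculation.

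**The concern.** The stated purpose and the actual need do not match. A difference in numbers between two groups is not a confounder. It affects only the standard error, which already allows for it. What can bias this comparison is a difference between the children of the two schools at the start, and the analysis section never gives that as the reason for adjusting.

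The consequence is practical. An analyst who follows the text could fit the change model with age, gender and pubertal stage only. If change in BMI z depends on its starting value, as regression to the mean would produce, a baseline gap between the schools would then enter the estimated effect. The trial was powered on change in standardized BMI, so this is the scale on which the omission matters most.

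**Working it through.** **Inputs from the protocol article.** All students: 438 experimental, 353 control. Students with excess weight: 138 and 125. Planned difference in change of standardized BMI: 0.12. Spread: 0.30 (called a standard error, but it works only as an SD). Alpha 0.05, taken as two-sided; power 0.80; stated size 98 per group.

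**The plan's own figure.** n per group = 2 × (1.960 + 0.842)² × (0.30/0.12)² = 2 × 7.849 × 6.25 = 98.1. This reproduces the stated 98 (99 if rounded up), so 0.30 can be used as the SD of change.

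**Do unequal sizes matter?** Efficiency relative to an equal split is 4ab/(a+b)²; the standard error is 0.30 × √(1/a + 1/b).

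| Sizes | Efficiency | SE | SE at equal split |
|---|---|---|---|
| 138 vs 125 | 69,000/69,169 = 99.8% | 0.03704 | 0.03700 |
| 438 vs 353 | 618,456/625,681 = 98.8% | 0.02146 | 0.02133 |

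Power for 0.12 at 138 vs 125 is 89.96%, against 90.03% for an equal split. In simulations with no effect and no baseline gap, the unadjusted comparison had bias of about 0 and type I error of about 5% at both pairs of sizes.

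**Does a baseline gap matter?** The article gives no baseline BMI z by school, so the following inputs are assumed:
- gap between schools in mean baseline z: 0.1 to 0.3
- slope of change on baseline: -0.1 to -0.3
- SD of baseline z among overweight students: 0.6

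With no treatment effect, the bias of the unadjusted difference in change is slope × gap. Its absolute size is:

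| Gap | Slope -0.1 | Slope -0.2 | Slope -0.3 |
|---|---|---|---|
| 0.1 | 0.01 | 0.02 | 0.03 |
| 0.2 | 0.02 | 0.04 | 0.06 |
| 0.3 | 0.03 | 0.06 | 0.09 |

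Against the planned 0.12 this runs from 0.01/0.12 = 8% to 0.09/0.12 = 75%. Simulation at 138 vs 125 (4,000 runs per cell) gave the same biases within sampling error, with type I error from 6.5% to 68%. With baseline z in the model, bias was at most 0.0014 and type I error 4.8% to 5.5%. The bias favours the intervention if the experimental school starts heavier and works against it if the control school does.

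**The case against.** **This is a condensed article, and full covariate lists usually sit in the analysis plan.** That excuses a short list. It does not excuse a stated purpose that is wrong, and the list that is given leaves out the most relevant covariate for the change model.

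**Baseline adjustment is partly planned.** The odds ratios do carry other baseline measures, which may include baseline BMI z. This stands for remission and incidence, where the request is only to name the variable. It does not cover the model for change. The broad set of baseline features belongs to the imputation model, not to the analysis model.

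**Stronger readings that the document does not support:**
- A reader might infer that the schools are already shown to differ, since excess weight is 138/438 = 31.5% in one and 125/353 = 35.4% in the other. The 3.9-point gap has z = 1.16 (p = 0.25), is compatible with chance, and says nothing about mean z among overweight students.
- A reader might infer that a small baseline gap would distort remission by several points. Assume baseline N(0.5, 1.2) truncated at z = 1, and SD of change 0.30. Remission falls from 9.9% to 6.4% only if 0.10 is added after truncation, so that no child in that school starts between 1.0 and 1.1. Both schools select at z ≥ 1, so that does not describe them. Shifting the school's mean by 0.10 before truncation gives 9.9% to 9.5%. Remission is also the outcome for which some baseline adjustment is planned.
- A reader might infer that socioeconomic equivalence cannot be checked or adjusted for, because the data come from outpatient visits. All overweight students in both schools are invited or referred to CREN, so the schools can be compared and adjusted among attenders. A separate form at parent meetings would depend on attendance too.

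**Conclusion.** The point holds for the model of change. The purpose given for covariate adjustment is mistaken, and baseline BMI z is not named where it is most needed. That group size is not the issue follows from the article's own numbers. The size of any bias does not: about 0.01 to 0.09 on a planned 0.12 rests entirely on the assumed gap and slope, and it would be zero if the schools started level or if change did not depend on baseline. For remission and incidence the defect is one of specification only. For socioeconomic status the limit is incomplete coverage, not absence of data. Even a fully specified model leaves school and treatment confounded, because each arm is a single school.

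**What to change.** - Replace the reference to a difference in sizes by baseline differences between the schools.
- In each model for change, include the baseline value of that outcome together with age, sex and pubertal stage.
- In the remission and incidence models, name baseline BMI z among the other baseline measures.
- Where the socioeconomic data collected at CREN are available, tabulate them by school, report how many students they cover, and use them in a sensitivity adjustment.
- State that covariate adjustment cannot separate the effect of the intervention from that of the school.

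The cost is a few sentences in the plan and one extra table. Baseline BMI z is already measured and the socioeconomic items are already being collected, so no new data are needed.
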